#### Health status

The Short Form Survey (SF-12) will be used to measure the health status of the participants. The total score ranges from 0 to 100 and a higher score indicates better health status. The SF-12 has been validated for use in TBI research [38]. The secondary outcome is the difference between groups in change in participation and health status over all time points, as measured by the total scores of the respective subscales of the USER-P and SF-12.

### Secondary process measures

#### Psychological flexibility

The Acceptance and Action Questionnaire II (AAQ-II) is a seven-item questionnaire measuring psychological flexibility. The items are scored on a 7-point Likert scale and the total score ranges from 0 to 49 with a higher score indicating more psychological flexibility. The internal consistency of the AAQ-II is good (Cronbach α = 0.84) [39]. Furthermore, the questionnaire has been validated in a sample of patients with ABI [40]. The Acceptance and Action Questionnaire after brain injury (AAQ-ABI) measures psychological flexibility about the thoughts and feelings related to the brain injury, while the AAQ-II measures psychological flexibility around general psychological distress. The AAQ-ABI consists of seven items, which are scored on a 5-point Likert scale. The score ranges from 0 to 36 with higher scores indicating greater psychological flexibility. The questionnaire has good internal consistency (Cronbach α = 0.89) [40].

#### Valued living

The Valued Living Questionnaire (VLQ) is a two-part instrument that measures valued living. First, the participant rates the importance of ten value domains on a 10-point Likert scale. Second, participants rate how consistently he or she has lived in accordance with their values within these domains. Scores from both parts are used to calculate a valued living component. The internal consistency of the valued living component has been demonstrated as adequate (Cronbach α = 0.74) [41]. The VLQ has been used in earlier research to measure valued living in patients with TBI [27].

#### Cognitive fusion

The Cognitive Fusion Questionnaire (CFQ-7) measures cognitive fusion on a 7-point Likert scale. Scores range from 0 to 49. The higher the score, the more fused one is with one’s thoughts. Earlier research has shown that the CFQ has good factor structure, validity, reliability, and stability over time [42]. The questionnaire has been validated in healthy individuals and in patients [42, 43]. The secondary process outcome is the difference between groups in change in psychological flexibility, valued living, and cognitive fusion over all time points, as measured by the total scores of the respective subscales of the AAQ-II, AAQ-ABI, VLQ, and CFQ-7.

### Personal and brain-injury-related characteristics and feasibility

Participants will fill out a demographic questionnaire at the start of the study. This questionnaire will register age, gender, employment, and education. Injury-related factors will be obtained from the medical files of the participants. These include type of brain injury, time since brain injury, severity of injury, and affected hemisphere of the brain. After ending the treatment, the participant’s opinion of and satisfaction with the ACT (treatment feasibility) will be questioned by means of a short semi-structured interview.

### Procedure

Participants will be recruited at participating hospitals and rehabilitation centers in the Netherlands. To prevent unnecessary burden, the psychologists will check the inclusion and exclusion criteria. If the patient is willing to participate the investigator will meet with the patient (at the patient’s home, the hospital, or the university, as preferred by the patient) to discuss the participation in the study and answer questions. If all is clear the informed consent form will be signed by the patient and the researcher (see Additional file 2). Subsequently, the first measurements will take place (T0) and the participant will be randomly allocated to the experimental group receiving ACT or to the active control group receiving psycho-education. The therapy sessions will be scheduled with the psychologist or healthcare professional. One month after the start of the intervention both groups will fill in the questionnaires for T1 (see Fig. 2). Questionnaires will be filled in on paper and measurements will be conducted by a research assistant blinded to allocation. After 3 months, when the treatment program is completed, the participants will fill in the questionnaires for T2. There will be follow-up measurements at 7 months (T3) and 12 months (T4). Again, these measurements will be conducted by a research assistant blinded to allocation. Research assistants will enter the data and data entry will be periodically checked during the monitoring visits. Follow-up appointments will be planned at the end of each visit. The research assistant will remind participants of their appointment by telephone or e-mail 1 week before the appointment is due. During the assessments, the researcher and research assistants will be alert for any adverse events such as suicidality. All adverse events related to mood complaints reported spontaneously by the subject or observed will be systematically collected and reported to the medical research ethics committee. Based upon these events the decision may be made to discontinue participation in the study. Furthermore, participants can leave the study without any consequences, at any time, for any reason if they wish to do so. The investigator can decide to withdraw a subject from the study for urgent medical reasons.

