### Ethical considerations and dissemination

Data will be handled confidentially and reporting will be coded. Each participant is given a personal code, which can only be linked to a person when the coding key is known. Collected data and personal information will be stored separately. The coded dataset will be available to the research team, healthcare inspectorate, study monitors, and members of the medical research ethics committee. The handling of personal data will comply with the General Data Protection Rule and the Research Data Management Code of Conduct of Maastricht University. Data will be used for future studies if the patient agreed upon this in the informed consent form. Data and material will be stored for 15 years in a repository of Maastricht University and can be made available to researchers upon request.

Participants will be compensated for any harm or injury due to participation in the study. The sponsor/investigator has liability insurance, which is in accordance with article 7 of the Medical Research involving Human Subjects Act. All adverse events will be followed until they have abated, or until a stable situation has been reached. Depending on the event, follow up may require additional tests or medical procedures as indicated, and/or referral to the general physician or a medical specialist. Any further treatment required for mood complaints after termination of the intervention will be arranged within the healthcare system. Adverse events will not be reported in the publication unless an adverse event occurs often and will, therefore, lead to a bias.

Ethics approval for the study has been given by the medical research ethics committee of Maastricht University Medical Centre and Maastricht University (committee reference number NL65349.068.18). Any protocol modifications will be communicated to the ethics committee. The study will be monitored by the Clinical Trial Centre Maastricht. In every site, there will be a site initiation visit, two monitoring visits, and a close-out visit. The monitoring will be performed independently of investigators and the sponsor.

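### Systematic collection is promised only for mood-related adverse events, while follow-up covers all events and publication is restricted, so a comparison of harms by arm is not secured

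*Protocol article*

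**What the plan says.** The protocol article deals with adverse events in two places.

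The Procedure section says that during assessments "the researcher and research assistants will be alert for any adverse events such as suicidality". The next sentence sets the collection rule: "All adverse events related to mood complaints reported spontaneously by the subject or observed will be systematically collected". The events so collected are "reported to the medical research ethics committee".

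The section Ethical considerations and dissemination sets two further rules. On follow-up: "All adverse events will be followed until they have abated, or until a stable situation has been reached". On publication: "Adverse events will not be reported in the publication unless an adverse event occurs often and will, therefore, lead to a bias".

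The article does not say how an adverse event unrelated to mood enters the record, and it mentions no comparison of adverse events between arms.

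**The concern.** Three rules that should share one definition do not. Staff watch for any event, systematic collection is promised for a subset, and follow-up is promised for everything. An event outside the subset can be followed, or counted as frequent, only if somebody noted it, and the text commits to systematic noting only within the subset.

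The filter also acts at the wrong moment. Relation to mood is a judgement about cause. Made before recording, it may leave no trace of a borderline event, so nobody can check the decision later. Made after recording, it is an attribute that can be reviewed.

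The Discussion looks to use in clinical practice for a large number of patients if the intervention proves effective. That case needs harms by arm as well as benefit, and harms counts support a comparison only if they were gathered alike in both arms.

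**Working it through.** No arithmetic applies. The plan gives no adverse event rate and no figure to reproduce, so the check sets the rules side by side.

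**Scope of each rule**

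- Vigilance at assessments (Procedure): any adverse event, with suicidality as the example.
- Systematic collection and ethics committee reporting (Procedure): events related to mood, found by spontaneous report or observation.
- Follow-up (Ethical considerations and dissemination): all adverse events, no mood restriction.
- Publication (same section): none, unless an event is frequent and leads to bias; no mood restriction.
- Withdrawal (Procedure): "The investigator can decide to withdraw a subject from the study for urgent medical reasons". The reason need not concern mood, so the event behind a withdrawal may lie outside the systematic record.

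**Do the rules fit together?** Follow-up and the frequency condition for publication both presuppose a record of all events. The collection rule commits to such a record for mood-related events only. For the rest, some noting is implied, but its method and completeness are not stated.

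**Can the filter be applied consistently?** The Introduction says that anxiety and depressive symptoms raise the number and severity of reported problems such as fatigue and headache. On that account, whether worsening fatigue is mood-related has no obvious answer, and the article gives no criterion.

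**Who might apply it?** The article does not name a judge. The people told to watch are the research assistants and the researcher. Under Randomization and blinding the assistants are blinded, but the researcher opens the envelope after T0 and reveals the allocation. Participants also know their arm, and collection depends on what they volunteer or staff notice. Unequal ascertainment is thus possible; the text does not show that it will occur.

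**What reaches the reader of the results?** The publication rule covers every adverse event, mood-related ones included. The article does not define how frequent an event must be or what bias is meant, so the decision would be taken once the data are known. Changing the collection rule alone would leave harms unpublished. Changing the publication rule alone would publish counts whose equal collection is secured only in part.

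**The case against.** The strongest defence has four parts.

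First, the article does not say that other events go unrecorded. Staff watch for events of any kind, and following all events implies that they are noted. This stands. A reader might infer that non-mood events are never counted, or that the arms cannot be compared on harms, but the documents do not support either statement. What they support is that equal, systematic collection of these events is not secured.

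Second, harms are measured in other ways. The HADS and DASS-21 are compared over all time points, so symptom worsening can be compared by arm. The EQ-5D-5L, SF-12 and cost questionnaire cover health status and care use. This also stands, and it rules out the further inference that the trial could not state the harms of either arm. None of these instruments is described as an adverse event record, however.

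Third, the article condenses a full protocol (version 8.0), which may hold forms and procedures for serious events. Silence on such detail would be no finding. Here the article is not silent: it states a restrictive rule that does not fit its own follow-up rule. One could read the follow-up promise as covering only events that came to notice, which softens the contradiction but leaves the scope unclear.

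Fourth, a focus on mood is reasonable for two talking or training interventions, and the assessors are blinded. The focus is defensible as an emphasis in analysis. It is weaker as a filter before recording. Blinding of the assistants does reduce the risk of unequal ascertainment; the unblinded researcher's share in the watching keeps some of it open.

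**Conclusion.** The point holds in this limited form. The two sections use different adverse event scopes and must be reconciled. As they stand, non-mood events have no stated systematic and equal collection in the two arms, mood relatedness is judged before recording, and the publication rule may withhold whatever is collected. The publication rule is the firmer obstacle to a comparison of harms, and it has to change together with the collection rule.

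The size cannot be expressed as a number. The rules affect all 94 planned participants over 12 months, but how many events would be missed or misclassified is unknown. The conclusion assumes that the article reports the collection rule faithfully. If the full protocol already records all adverse events alike in both arms, correcting the article's wording settles the collection part, and the publication rule still needs to change.

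This is a worthwhile, inexpensive improvement and does not undermine the efficacy comparison.

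**What to change.** - In Procedure, set one scope for recording: all adverse events and serious adverse events, whatever their presumed cause.
- Have the blinded research assistants ask the same open question at T1, T2, T3 and T4 in both arms, and record spontaneous reports and observations on the same form.
- Classify mood relatedness after recording, by a stated criterion and by someone unaware of the allocation. State separately which recorded events go to the ethics committee.
- In Ethical considerations and dissemination, use the same definition for follow-up, and replace the publication rule with reporting of adverse events by arm.
- Recruitment began on 24 April 2019. Introduce the change in both arms on one date and report which visits fell under which rule.

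The cost is one question and one form at four visits that already take place, plus some added recording and reporting. Two limits remain. The later visits look back over four months (3 to 7) and five months (7 to 12), so recall will be imperfect, though alike in both arms. An open question may also prompt a participant to mention the treatment; the existing request not to do so should be repeated when it is asked.

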**Fig. 2 Fig2:**
[figure not shown]
Standard protocol items: recommendation for interventional trials (SPIRIT) diagram

### Interventions

#### BrainACT intervention

The ACT intervention involves eight weekly individual sessions of 60 min during a period of 3.5 months. The first four sessions are weekly, thereafter the sessions will be biweekly, with a 3-week break between the seventh session and last session. Participants will do homework exercises of around 30 min for 6 days a week. Homework consists of reading or listening to summaries of the sessions, practising skills, and doing mindfulness exercises. At the start of the intervention, participants will receive a workbook with instructions that they can read at home after each session. We use an eight-session protocol (see Table 1) based on Jansen and Batink [44], Luoma, Hayes, and Walser [45], and Whiting et al. [31] in which all six ACT core processes are addressed. Psychologists are free to decide on the order of the sessions. We altered the treatment for people with ABI as suggested by Kangas and McDonald [24] and Broomfield et al. [46]. An expert group of psychologists experienced in ACT and/or in working with people with ABI gave further advice on the alterations. The possible cognitive deficits of the participants are taken into account and brain-injury-related topics are discussed during the treatment. A treatment protocol is specified to ensure comparability of the ACT intervention across settings. The intervention will be provided individually by certified psychologists who completed an ACT training course of at least 5 days and are experienced in working with patients with ABI. The therapy will take place at hospital outpatient facilities.

**Table 1 Tab1:** Overview of the BrainACT treatment programme

Topic	Content
Values	Value exploration and difference between goals and actions
Committed action and Mindfulness	Committed action on the long and short term in relation to values, education about mindfulness, and practising contact with the present moment
Effect of control	Creative hopelessness; the undeniability of human suffering and the long-term consequences of trying to control it
Acceptance	Introducing acceptance as an alternative to control
Defusion	Changing the relationship with thoughts, naming the mind
Self-as-context	Changing the relationship with thoughts about oneself and introducing the constant self
Defusion and Mindfulness	Review and exercises on defusion and mindfulness
Psychological flexibility	Review of the different core components, explanation on how these skills together lead to psychological flexibility, and preparation on relapse and setbacks

#### Active control intervention

The control condition (see Table 2 for an overview) consists of an eight-session psycho-education intervention combined with relaxation training with a duration of 1 h. A Cochrane review concluded that active information provision is able to reduce depression and anxiety after brain injury [47]. Furthermore, earlier research has shown that relaxation exercises reduce post-stroke anxiety [48]. The psycho-education is based on the existing module *Niet rennen maar plannen* (don’t run, plan) [49], which is a training and education programme focussing on cognitive rehabilitation for patients with brain damage and mild cognitive problems. The intervention aims to offer information and education about brain injury and its consequences. Relaxation exercises consist of progressive muscle relaxation [50] and autogenic training [51]. Participants will do homework exercises of around 30 min for 6 days a week. A treatment protocol is specified to ensure comparability of the education intervention across settings. This intervention will be provided individually by a healthcare professional with experience in working with patients with brain injury (e.g. psychologist, social worker, occupational therapist, psychological assistant, but not the psychologist providing the ACT intervention) at hospital outpatient facilities.

**Table 2 Tab2:** Overview of the psycho-education and relaxation treatment program

Session number	Content
1	Psycho-education on the basic functions of the brain and causes of brain injury
2	Psycho-education on relaxation training and a progressive muscle relaxation exercise
3	Psycho-education on the consequences of brain injury and a progressive muscle relaxation exercise
4	Psycho-education on changes in behaviour and mood following brain injury and an autogenic training exercise
5	Psycho-education on fatigue following brain injury and an autogenic training exercise
6	Psycho-education on memory problems following brain injury. Participants can choose between autogenic training or a progressive muscle relaxation exercise. This technique will also be used in the following sessions
7	Psycho-education on information processing and planning and an autogenic training exercise or a progressive muscle relaxation exercise
8	Review of the different sessions, wrap up, and an autogenic training exercise or a progressive muscle relaxation exercise

### Sample size calculation

The sample size calculation was performed using G*Power based on a repeated measures design. With a large effect size of 0.4, alpha value of 0.05, power value of 0.80, two groups (intervention and control), and five measurements, at least 80 participants are required. With an expected drop-out rate of 15%, 94 participants need to be recruited.

### Statistical analysis

The statistical analysis can be divided into four parts. First, the baseline characteristics will be described. Second, between-group differences at baseline will be analysed using the chi-square test and independent samples *t* test to verify the success of randomization. Furthermore, groups will be compared on primary outcome measures at T2 using the chi-square test and independent sample *t* test. Linear mixed models for repeated measures will be used to study the differences between groups with the primary and secondary outcome measures as dependent variables. Models will include main effects of the intervention (ACT or psycho-education) and time (T0, T1, T2, T3, and T4) as categorical variables and the interaction effect of intervention and time. Baseline-adjusted mean differences between groups at each time point with 95% confidence intervals will be calculated. The effects of the intervention will be analysed according to the intention-to-treat principle. Alpha will be set at 0.05. All quantitative analyses will be conducted using SPSS software version 25 [52]. Clinically significant change will be determined on the primary outcome measures [53] to gain insight into clinical improvement on an individual level. The first step is to identify patients who “recovered” by using the cut-off scores of the primary outcome measures (HADS and DASS-21). The second step is to calculate the reliable change index, which identifies the patients with a significant improvement. Patients who both recovered and showed a significant improvement will be considered clinically significantly improved. The number of clinically significantly improved patients will be compared between interventions. The trial-based economic evaluation will involve a combination of cost-effectiveness analysis and cost-utility analysis.

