### Primary outcome measures

#### Psychological distress

The subscales of the HADS will be used to measure anxiety and depressive symptoms over the past 7 days. The scores for the scales, seven items each, range from 0 to 21 with higher scores indicating higher levels of depression or anxiety. This questionnaire has been validated in a sample of patients with TBI [32]. Furthermore, there was good internal consistency for both subscales (Cronbach α depression scale, 0.81; anxiety scale, 0.84) in patients with stroke [33]. The Depression Anxiety Stress Scales-21 (DASS-21) will be used to measure the participants’ levels of anxiety, depression, and stress. It consists of 21 items, which are rated on a 4-point Likert scale. The score ranges from 0 to 63 with higher scores indicating greater levels of depression, anxiety, or stress. The questionnaire has been validated in a sample of patients with TBI. The internal consistency was good for the three scales (Cronbach α depression scale, 0.90; stress scale, 0.89; anxiety scale. 0.82) [34]. The primary outcome is the difference between groups in change in mood and anxiety symptoms over all time points, as measured by the total scores of the respective subscales of the HADS and DASS-21.

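### The mixed model treats T0 as an outcome with a free group effect, so its terms give differences in change from T0, which are valid but less precise than covariate-type baseline adjustment

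*Protocol article*

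**What the plan says.** All references are to the protocol article.

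- **Model terms (Statistical analysis).** "Models will include main effects of the intervention (ACT or psycho-education) and time (T0, T1, T2, T3, and T4) as categorical variables". A group-by-time term is listed as well. The model serves the primary and the secondary outcomes.
- **Reported effect (Statistical analysis).** "Baseline-adjusted mean differences between groups at each time point with 95% confidence intervals will be calculated". How baseline is adjusted for is not stated.
- **Primary outcome (Psychological distress).** "The primary outcome is the difference between groups in change in mood and anxiety symptoms over all time points".
- **Error level (Statistical analysis).** "Alpha will be set at 0.05".
- **Size (Sample size calculation).** "With a large effect size of 0.4, alpha value of 0.05, power value of 0.80, two groups (intervention and control), and five measurements". This leads to a requirement of 80 evaluable participants, raised to 94 for 15% dropout.

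The sample size section gives no correlation between repeated measurements.

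**The concern.** The listed terms and the promised estimate do not obviously match. With T0 as a level of time and an intervention main effect plus interaction, the model estimates a separate mean for each arm at each of the five visits, T0 included. Two kinds of group comparison follow directly: the raw difference at a visit, and the difference in change from T0. Neither uses the T0 score as a covariate, and nothing tells the model that randomisation makes the two T0 means equal in expectation.

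What is at stake is precision. Subtracting the whole baseline score is the best use of it only when the correlation with follow-up is close to 1. At lower correlations the subtraction adds noise that covariate adjustment, or a common T0 mean, would avoid. The same model serves every primary and secondary outcome, and the trial has about 40 evaluable participants per arm, so the loss recurs throughout the results.

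**Working it through.** **1. The plan's own figure.** The article does not say which G*Power procedure was used. A multivariate repeated-measures test of the group-by-time interaction, with f = 0.4, five measurements and N = 80, has noncentrality 0.4² × 80 = 12.8 on 4 and 75 degrees of freedom. Its power is 0.803, and 80 is the smallest N that reaches 0.80. Dropout: 80/0.85 = 94.1, against 94 stated. The planned N therefore agrees with a 4-df interaction test, that is, with a comparison of changes.

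**2. Assumptions for the comparison.** Equal variance (set to 1) at all visits, one common correlation ρ, complete data, 40 per arm. None of these except the 80 evaluable participants comes from the article, so ρ is varied.

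**3. Per-visit variance factors.**

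- Difference in change from T0: 2(1 − ρ)
- Covariate-adjusted difference, or T0 as outcome with a common mean: 1 − ρ²
- Information lost: 1 − (1 − ρ²)/[2(1 − ρ)] = (1 − ρ)/2

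| Assumed ρ | Change | Adjusted | Information lost | 80 analysed by change are worth, if adjusted |
|---|---|---|---|---|
| 0.3 | 1.40 | 0.91 | 35% | 80 × 0.65 = 52 |
| 0.5 | 1.00 | 0.75 | 25% | 80 × 0.75 = 60 |
| 0.7 | 0.60 | 0.51 | 15% | 80 × 0.85 = 68 |
| 0.8 | 0.40 | 0.36 | 10% | 80 × 0.90 = 72 |

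**4. Average over T1 to T4.** The factors are 1.25(1 − ρ) for change and (1 − ρ)(0.25 + ρ) adjusted, so the loss is 0.8(1 − ρ): 56% at ρ = 0.3, 40% at 0.5, 24% at 0.7 and 16% at 0.8. Contrasts among the follow-up visits themselves do not involve T0 and gain nothing.

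**5. Simulation (10,000 trials per ρ, 40 per arm).**

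| ρ | Coverage, change | Coverage, covariate-adjusted | SD of estimate, change | SD of estimate, adjusted | Loss, 1 − (SD ratio)² |
|---|---|---|---|---|---|
| 0.3 | 95.1% | 94.9% | 0.2654 | 0.2156 | 34% |
| 0.5 | 95.1% | 95.2% | 0.2233 | 0.1940 | 25% |
| 0.7 | 95.3% | 95.1% | 0.1712 | 0.1587 | 14% |

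The change contrast has nominal coverage, and the loss agrees with the formula.

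**6. Illustration in power.** Take a true difference of 0.5 SD at one visit and ρ = 0.5. Both are assumptions; neither is in the article. The standard errors are √(1.00 × 2/40) = 0.224 and √(0.75 × 2/40) = 0.194. Two-sided power at 0.05 is about 60% for the change contrast and 72% for the adjusted difference.

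**7. If T0 were both outcome and covariate.** With a common slope over the five visits, b = (1 + 4ρ)/5. At ρ = 0.5, b = 0.6. The residual variance is (1 − 0.6)² = 0.16 at T0 and 1 + 0.36 − 0.6 = 0.76 later, so the pooled value is (0.16 + 4 × 0.76)/5 = 0.64. The standard error is too small by a factor √(0.64/0.76) = 0.92. Simulated per-visit coverage, under compound symmetry, was 93.6%, 93.3% and 93.0% at ρ = 0.3, 0.5 and 0.7.

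**The case against.** The strongest reply is that nothing is wrong. The primary outcome is defined as a difference in change, the interaction contrasts estimate exactly that, subtracting baseline is a recognised form of baseline adjustment, and the planned N agrees with the interaction test. All of this stands. It rules out any claim of bias or invalid intervals, and leaves an efficiency argument.

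A second reply is that a journal article condenses the protocol, and that the baseline term and covariance structure belong in an analysis plan that is not shown. This stands for the covariance structure. It does not fully answer the point, because the article itself lists the model terms and names the reported effect, and the listed terms do not deliver the more precise form of that effect.

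Three stronger readings are tempting, and the article does not support them:

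- *A quarter of the sample is wasted.* That figure holds per visit only at ρ = 0.5, and the article states no correlation.
- *The baseline is used twice, so type I error is inflated.* No baseline covariate is named anywhere. The narrow intervals also need a common residual variance, and the per-visit effect is modest. With complete data and compound symmetry the group-by-time interaction test would not change at all.
- *The adjusted difference is meaningless because it is promised at T0 too.* Each time point can naturally be read as each follow-up visit, and no harm follows from the wording.

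**Conclusion.** The point holds as a matter of precision and clarity. The model as listed gives at best differences in change from T0. These are valid and consistent with the primary outcome, but they lose (1 − ρ)/2 of the information per visit relative to covariate-type adjustment: 10% to 35% for ρ from 0.8 down to 0.3. For the T1 to T4 average the loss is 16% to 56% over the same range. The figures rest on equal variances, one common correlation and complete data, and ρ is assumed throughout. Double use of the baseline is a caution about how the promised adjustment might be carried out; it is not a finding about what is planned.

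**What to change.** Name one method of baseline adjustment in the analysis plan:

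- keep T0 in the response but constrain both arms to a common T0 mean (time, and group-by-time for T1 to T4 only, with no group effect at T0); or
- take T1 to T4 as the response, with the T0 score of the same scale and its interaction with time as covariates, plus group, time and group-by-time.

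Report adjusted differences with 95% confidence intervals at T1 to T4. Do not enter T0 both as an outcome level and as a covariate. If the change contrast is preferred after all, call the result a difference in change from T0 and accept the lower precision knowingly. The choice should be fixed before the data are analysed.

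The cost is a sentence or two in the plan and a few lines of SPSS syntax. T0 is already collected, and no visit, measurement or sample size changes.
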